## **1. Background and rational**

### **1.1 Need for clinical research and epidemiologic transparency**

There is substantial agreement that well conducted and reported randomised controlled trials (RCTs) generate the most trustworthy evidence when newly developed or already existing clinical interventions are evaluated (1-3). Besides the complexity and the high associated costs of conducting RCTs (4-6), there are major issues with their reporting that often make it difficult for researchers, clinicians, patients or policymakers to interpret the current evidence on a specific topic (7, 8). Chronologically, the most prominent difficulties in reporting consist of (i) poor reporting in study protocols for RCTs (9-12); (ii) a substantial fraction of trials are not registered, prematurely discontinued (most common due to difficulties with recruitment) and not published (13, 14); and (iii) that published RCTs are often poorly reported (7).

For clinicians, scientists and decision makers, published articles are often the only way to know how a study was conducted. In order to judge the internal and external validity of RCTs, it is crucial that these articles present transparent, accurate and unbiased information about the methods and conduct of the RCT.

### **1.2 Transparency in published randomised controlled trials**

To improve the transparency in clinical and epidemiological research the international organisation called the EQUATOR (Enhancing the Quality and Transparency of Research) Network was founded in 2006 (15-20). This international network consists of researchers, epidemiologists, people in charge of recommendations for the presentation of articles or “reporting guidelines”, statisticians, clinicians and editors from some of the most prestigious journals (e.g., *Lancet*, *JAMA*, *Annals of Internal Medicine*, *BMJ*).

The CONSORT Statement (CONsolidated Standards for Reporting Trials), is perhaps the most important reporting guideline designed to help improve the transparency and quality of reporting of RCTs (21, 22). The CONSORT Statement, consisting of 25 items and a flow diagram which should be reported in papers describing RCTs. The last update of the CONSORT Statement was published simultaneously in 10 leading medical journals in 2010 (23). Currently CONSORT is endorsed by 585 journals (24). The CONSORT Statement guides authors, peer reviewers and journal editors on what information should be included in published reports of RCTs in order to facilitate critical judgment and interpretation of results. It is important to note, that adhering to the CONSORT Statement does not mean that the study is of high quality. However, reporting all items from the CONSORT list will enable readers to adequately judge the quality of RCTs.

A number of research studies have identified serious limitations in the reporting of published RCTs (3, 25-30). Despite some improvement in reporting following the implementation of the CONSORT Statement, there still remain major reporting deficiencies in published RCTs (31). For example, Ouditayo and colleagues showed that a large proportion of RCTs published in December 2012 in PubMed did not define the primary outcome (31%), did not state the sample size calculation (45%) and did not explain the method of allocation concealment (50%) (32). This lack of transparency is a major limiting factor for the reader who assesses an article in order to find the answer to a specific question; it is also a major problem for scientists who perform systematic reviews and meta-analyses. Thus, some published trials may not be included in the meta-analysis because of their lack of transparency. Chan showed (25, 33) that 50% of efficacy outcomes and 65% of safety outcomes could not be included in meta-analyses because of how they were reported. Furthermore, even if these trials are included in systematic reviews and meta-analyses, an adequate risk of bias assessment is often not possible due to the poor reporting quality. Nevertheless, the main consequence of the lack of transparency is the risk of accepting treatments that are ineffective or cause serious adverse events (34).

### 1.3 Journal attempts to improve reporting in published randomised controlled trials

Journals can play a vital role in improving the reporting of published reports of RCTs. For example, a survey of authors' instructions on journal websites revealed that in 2014 63% (106 of 168) of biomedical journals mentioned CONSORT within their "Instructions to Authors" (35). Of those journals 38 (36%) required a CONSORT checklist as a condition of RCT report submission. Such implementation indicates some improvement over time compared to an assessment in 2007 when only 17 journals requested the CONSORT checklist (36). An interrupted time series analysis which assessed if the CONSORT for Abstracts guideline had an effect on the reporting quality, found that results are better reported in Journals which enforce the policy (37).

In a study published in 2016 authors of RCTs were asked by journal editors to use the web-based CONSORT tool at the manuscript revision stage (38). Authors who were randomly allocated to the intervention had access to a tool which allowed them to combine different CONSORT extensions (according to study design, medical field) to generate customised checklists. In the control group, authors had access to a CONSORT flow diagram generator. The goal was to improve the reporting of CONSORT items with a simple webtool. However, a quarter of all authors either wrongly selected a CONSORT extension or failed to select an extension, indicating that further education is needed in terms of when and how to implement CONSORT extensions.

## **2. Hypothesis**

We propose an RCT to evaluate the impact of asking peer reviewers to use a short version of the CONSORT checklist when reviewing a manuscript of an RCT and whether it improves the completeness of reporting. Our hypothesis is that reminding peer reviewers of the CONSORT items (including a short explanation of those items) will result in higher adherence to CONSORT guidelines in published RCTs. We only selected a limited number of the CONSORT items because we did not want to deter peer reviewers with too much information. Since peer reviewing in general can be burdensome, we felt that this approach is more promising than listing all items, risking that the information will be ignored. The short version of the CONSORT checklist is based on the same items described in a previous study as the 10 most important and underreported CONSORT items (38).

## **3. Objective**

### **3.1 Main objective**

The main objective of this study is to evaluate the impact of asking peer reviewers during the standard peer-review process to ask them to use a short version of the CONSORT checklist (C-short) and whether it will improve the reporting in published RCTs compared to manuscripts where the peer reviewers underwent usual practice.

## 4. Methods

### 4.1 Trial design

This study is a multicentre RCT with articles being the unit of randomisation (Figure 1; allocation ratio 1:1). A multicentre parallel arm RCT with randomisation at the individual article level was chosen instead of a cluster RCT because the risk of any “contamination” on journal level is not given as the intervention will be implemented by an external researcher (i.e. BS). The possibility of contamination due to the possibility that peer reviewer are invited to assess several RCTs and are randomised into both arms was judged as relatively small and therefore we do not plan to adjust for clustering by journal. The journal staff (i.e. editors) will not be actively told which manuscript was allocated to the proposed intervention and which to the control group.

**Figure 1:** Study flowchart

[figure not shown]

### 4.2 Study setting and eligibility criteria

The population will be defined on two levels. Included journals and included articles.

Included journals must: i) endorse the CONSORT Statement (e.g. assessed via journals Instruction to Authors); ii) publish primary results of at least five RCTs in 2017 (identified in a brief PubMed search as publishing RCTs in 2017). To be efficient, we plan to contact (via

email) the editors of eligible journals within a publishing house (i.e. journals which are part of the BMJ series, BMC series, PLoS, Lancet, JAMA) instead of separate journals. A description of the requirements for participation and a short summary information sheet will be included as part of the email invitation sent to journal editors. If a journal is eligible, and agrees to take part, the journal will also need to provide access to their journal editorial system (e.g. ScholarOne, Editorial Manager) to enable the external researcher (i.e. BS) to screen and randomise eligible manuscripts. In cases this is not possible, we will explore with separate journals if it would be possible to grant limited access (e.g. only rights to screen studies) and that the emails from the intervention would be sent by a person from the editorial team.

We will include all submitted manuscripts reporting RCTs for which the journal decides to send out for external peer review. Since the 10 chosen CONSORT checklist items are applicable to different study designs, we will include all RCTs regardless of study design (e.g. parallel group trial, cluster trial, superiority trial, non-inferiority trial). Articles presenting clearly secondary trial results, additional time points, economic analyses, or any other analyses derived from an RCT dataset not including the study's main results will be excluded. Furthermore, RCTs which are clearly labelled as a pilot or feasibility study or randomise animals or cells instead of individuals will be excluded.

Details of journal manuscript submission and peer review processes, including, consent and potential confidentiality issues will be discussed in detail with each journal by teleconference and/or face to face prior to the journal agreeing to take part to ensure that randomisation of manuscripts is feasible. We considered conducting randomisation at the level of the journal (i.e. cluster RCTs). However, in order to make the intervention as easy and simple to implement (and with little or no additional effort from the journal) we believe that randomisation at the manuscript level - with an external researcher implementing the intervention within the existing journal management systems - will be the most efficient study design.

In participating journals, the external investigator (BS) will have access to the editorial management software (e.g. ScholarOne or Editorial Manager) and will check at least twice a week (using automated report lists) all research manuscripts that are sent out for external peer review. As soon as the first peer-reviewer accepts the invitation to review, the manuscript will be randomised to the intervention or control arm (see "Randomisation" for more details). It is possible that this process might be slightly different amongst different included journals.

#### 4.3 Interventions

#### Experimental group: C-short plus usual practice

After accepting to review an article, peer reviewers will receive the automated, journal specific standard email with general information as per each journal's usual practice (e.g. where to access the manuscript, date when the peer review report is due). In addition, peer-reviewers who received a manuscript which was randomised to C-short will receive an additional email including a short version of the CONSORT checklist (C-short) (either within the email or as an attachment; based on the preferences and possibilities of the journal) focusing on the 10 most important and most poorly reported items (Table 1; as previously defined by a group of experts of the CONSORT Group (38)). Peer-reviewers will be asked to pay particular attention to items in the C-short checklist and request authors to report on these items, if not already adequately reported. This second email, containing the C-short checklist, is not generated automatically within the existing journal editorial management system (e.g. ScholarOne or Editorial Manager); it will be sent by the investigator who has access to the journal editorial system (BS). An example of this additional email is presented within the appendix (appendix 1; the exact wording might be changed according to the preferences of the participating journals). At least twice a week the editorial management system will be checked for each journal and if a peer reviewer has accepted an invitation to review, an email containing the C-short intervention will be generated and sent. It might be possible that some journals will only provide the right to access and read manuscripts in the editorial management system, but not to send emails. If this is the case, the corresponding Editor (or designated person within the journal) will be informed to send the emails.

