#### 4.7 Randomisation and blinding

Articles, which meet the eligibility criteria as a primary report of an RCT, for which the journal decides to send out for external peer review will be randomised into one of the two groups (allocation 1:1). The randomisation list will be created by the study-randomizer system (43) using random block sizes between 2 and 8 and stratification by journal. As soon as the first peer-reviewer accepts the invitation, the manuscript will be included and randomised to one of the two intervention arms. One of the investigators (BS) will log onto the study randomizer-system (43) entering the study identification number (ID; provided from the Journal), the study title, as well as the journal the study was submitted to. Subsequently, all additional peer-reviewers accepting the invitation to review the same manuscript will receive the same intervention (C-short plus usual practice or usual practice only) as the first peer-reviewer.

Authors will be blinded to the intervention allocation. Editors will not be actively informed about the randomisation (possible exception listed under “4.3 Interventions”). To avoid potential bias, peer reviewers and manuscript authors will not be informed of the study hypothesis, design and intervention.

Outcomes will be assessed in duplicate (see assessment of outcomes). At least one outcome assessors will be blinded. Due to restricted resources it might be possible that the investigator conducting the randomisation (BS) will be included in the data-extraction from published manuscripts.

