#### 4.7 Data management and confidentiality

Outcomes from publications will be assessed and extracted in duplicate. Since this information is not confidential, we will use Google Forms for data extraction from published RCTs. Data entered will be validated for completeness.

Data from the editorial manager software (e.g. Title of manuscript, first author, randomisation ID, Journal, date when manuscript was accepted by and academic editor, date when the final decision was made, final decision, number of peer-reviewers who peer reviewed the manuscript, the peer review) will be extracted, anonymised and entered in a password protected database which is saved on a server from the University of Oxford. Data will be managed and curated according to University of Oxford regulations, which includes regular back-up (on a daily basis) of the virtual drives where the data are stored.

The raw data extracted from the included manuscripts can be made openly accessible in an anonymised way (i.e. giving the included RCT a number instead of identifying them). Derived/aggregated data, including anonymised information generated from the journals' editorial manager software, will be stored and made available to the research community when the project ends (see also "8. Publication policy and access to data"). Where appropriate, the researcher who has access to the editorial manager software (BS) and anyone else who will see the identifiable data will sign a confidentiality agreement with the participating journals, confirming that they will not share identifiable data with any other party. Journals such as the BMJ series state in their Company Privacy Statement that research programmes for quality improvement might be in place. Furthermore, peer reviewers for all BMJ journals receive the following statement in their invitation letter *"We are constantly trying to find ways of improving the peer review system and have an ongoing programme of research. If you do not wish your review entered into a study please let us know by emailing [...] as soon as possible."*

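### Nothing stops a manuscript being randomised after its first review is already in, so some C-short prompts may come too late and slightly dilute the effect

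*Protocol*

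**What the plan says.** **Trigger for randomisation.** Section 4.2: "As soon as the first peer-reviewer accepts the invitation to review, the manuscript will be randomised to the intervention or control arm". Section 4.7 (Randomisation and blinding) repeats it: "As soon as the first peer-reviewer accepts the invitation, the manuscript will be included and randomised to one of the two intervention arms". Neither sentence makes allocation depend on whether a report has already arrived.

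**How acceptances are found.** Section 4.2 says the external investigator "will check at least twice a week (using automated report lists) all research manuscripts that are sent out for external peer review". Section 4.3 uses the same rhythm for the email: "At least twice a week the editorial management system will be checked for each journal and if a peer reviewer has accepted an invitation". The condition for sending is only that acceptance: "if a peer reviewer has accepted an invitation to review, an email containing the C-short intervention will be generated and sent".

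**How the email goes out.** It "is not generated automatically within the existing journal editorial management system". Where the investigator cannot send emails, "the corresponding Editor (or designated person within the journal) will be informed to send the emails". No time limit is given for either route.

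**Who is excluded and who is analysed.** The exclusions in 4.2 concern secondary reports, pilot or feasibility studies, and trials in animals or cells. None concerns review status. Section 4.8.1 takes as its main population every randomised manuscript that is accepted.

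**What is recorded.** Section 4.7 (Data management and confidentiality) gives examples of the data taken from the editorial system, among them "date when manuscript was accepted by and academic editor, date when the final decision was made, final decision", the number of reviewers and the review itself. The examples name no date of reviewer acceptance, C-short email or report.

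**The concern.** Immediate allocation does not fit a schedule that guarantees only two looks a week. Several days can pass between acceptance and the email, and more where an editor has to act. A quick reviewer can submit within that gap. Read literally, the protocol still randomises that manuscript and still emails that reviewer, and the article counts as a full member of the C-short arm.

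A prompt that reaches a reviewer after the first-round report has little chance to change that report. The observed difference would shrink towards zero, and a null result would be harder to attribute to the prompt itself rather than to the sending schedule. The sample size in 4.6 has almost no slack to absorb this.

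**Working it through.** **1. The plan's own figure.** Section 4.6, scenario 2 (adopted): 71% v 82%, difference 0.11, SD 0.25, two-sided 5% t-test, 80% power. Standardised difference 0.11/0.25 = 0.44. The exact two-sample t-test needs 82.05 per arm, rounded up to 83, so the stated 166 is reproduced. Power with 83 per arm is 80.5%.

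**2. Delay at the minimum frequency (assumption: gaps of 3 and 4 days, acceptances uniform over the week).** Mean delay = (3²/2 + 4²/2)/7 = (4.5 + 8)/7 = 1.79 days; maximum 4 days.

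**3. Share of reviewers who report before the email.** The protocol gives no review times, so the distribution is assumed: gamma, cumulative distribution F, means of 10, 14 and 21 days.

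Late share f = [∫₀³ F(t)dt + ∫₀⁴ F(t)dt] / 7

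| Mean review time | Shape 2 | Shape 3 | Shape 4 | Shape 1 (exponential) |
|---|---|---|---|---|
| 10 days | 6.1% | 2.8% | 1.5% | 15.9% |
| 14 days | 3.4% | 1.2% | 0.5% | 11.7% |
| 21 days | 1.7% | 0.4% | 0.1% | 8.0% |

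Under the exponential, the likeliest moment to report is straight after accepting, which is implausible for refereeing a trial. Shapes 2 to 4 give about 0.1% to 6%.

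**4. Sensitivity to the distribution and the spacing.** With log-normal times (median 7 to 14 days, log-SD 0.5 to 0.7), a 4-day gap gives 0.1% to 6.2%. A log-SD of 1.0, which is more variable than the exponential (SD/mean = √(e − 1) = 1.31 against 1), raises the top to 11.7%. The protocol does not fix the spacing of the checks. For acceptances falling in a 6-day gap, log-SD 0.5 to 0.7 gives 0.8% to 14.6%.

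**5. Effect on power, 83 per arm.** There are two bounding assumptions.

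*Effect proportional to the share prompted in time:* difference = 0.11 × (1 − f).
- f = 0.1%: 0.1099, power 80.4%
- f = 3.4%: 0.1062, power 77.7%
- f = 6.1%: 0.1033, power 75.4%

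*One timely reviewer is enough (assumption: two independent reviewers):* difference = 0.11 × (1 − f²).
- f = 6.1%: f² = 0.37%, difference 0.1096, power 80.2%
- f = 0.1%: no visible change, power 80.5%

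**The case against.** Several points against this carry weight.

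- Twice a week is a stated minimum, and 4.2 allows the process to differ somewhat between journals. The immediate-allocation wording can be read as naming the trigger, with the checks as the means of acting on it. Table 2 only places allocation after the first acceptance and does not claim immediacy. This softens the contradiction but does not supply the missing rule.
- A reader might infer that C-short reviewers *are* prompted late. The documents do not show this, because they contain no turnaround times. It is a possibility the wording leaves open.
- A reader might take losses of 12% to 16% of prompts, and power near 70% or lower, as the expected size. At these check gaps those figures need the exponential case or something more variable, and they treat each late reviewer as a lost share of the article. Section 4.7 sends C-short to every later reviewer too, so one late reviewer usually leaves the article partly exposed.
- A late prompt is not always useless. The outcome is read from the published article, and a reviewer who sees a revision can still act on it.
- A reader might say late delivery could never be detected. The data list in 4.7 is introduced as examples and includes the review itself, 4.4 plans to look for references to CONSORT in reviewer comments, and the investigator works inside the system that may hold the dates. They are simply not named.
- A reader might call the comparison biased or the sample size wrong. Neither holds. Allocation does not depend on report timing, and 83 per arm is correct for its assumptions.

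What stands is that the protocol does not say what happens when a report is already in at the check, and that this is an eligibility question to be settled before allocation.

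**Conclusion.** The point holds as a modest, cheaply closed gap. Sections 4.2, 4.3 and 4.7 together allow a manuscript to be randomised after its first review has been submitted, and 4.8.1 then analyses it if it is accepted. Any effect is dilution towards the null.

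Under the assumed review times (gamma, means of 10 to 21 days, shapes 2 to 4, checks 3 and 4 days apart), about 0.1% to 6% of reviewers would be prompted late. Power would drop from 80.5% to between about 80% and 75% under proportional dilution, and by 0.3 points at most if one timely reviewer of two suffices. Widely spaced checks or slow forwarding by an editor would increase the late share; neither can be sized from the protocol. The conclusion that the rule is missing does not depend on any of these figures.

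**What to change.** **Main change.** In 4.2 and in 4.7 (Randomisation and blinding) add: *A manuscript is randomised only if no review report has been submitted at the time of the check.* The rule is applied before allocation, so it acts identically on both arms and introduces no bias. Reword the immediate-allocation sentences in both sections to say that randomisation takes place at the first check after acceptance.

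**Also.** Name the dates of reviewer acceptance, C-short email and report among the data extracted for each reviewer, and report the share of C-short reviewers emailed before they reported.

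**Cost.** One eligibility sentence and three dates per reviewer. A few manuscripts are lost before randomisation. This costs some recruitment time but no power, since 4.6 continues recruitment until 83 articles are published in each arm.

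**Limit.** The rule does not reach later reviewers who report before their own email, or delay at a journal where an editor sends it. The recorded dates would show how often either happens. More frequent checks would reduce both the delay and the late share, but they are a workload choice for the investigator and are optional.

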## 4.8 Statistical methods

### 4.8.1 Populations of analysis

The main population for analysis will be all manuscripts randomised and accepted for publication in the participating journals. Differently from RCTs conducted with patients, where drop outs need to be carefully considered (e.g. multiple imputation of missing data), we are only interested in the reporting adherence of RCTs that are published. All outcomes will be calculated based on the main population for analysis. The secondary outcome "Time to the first decision", will additionally be calculated considering all randomised manuscripts (including the ones which were not published).

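### At journals giving read-only access, someone on the editorial side learns which manuscripts are in the C-short arm and sends the checklist, and nothing separates that person from decisions on the manuscript

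*Protocol*

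**What the plan says.** The general rule is that the external researcher sends the C-short email from inside the journal's editorial system. Protocol 4.1 rests the choice of manuscript-level randomisation on this: the risk of contamination "on journal level is not given as the intervention will be implemented by an external researcher". The same section adds: "The journal staff (i.e. editors) will not be actively told which manuscript was allocated to the proposed intervention".

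The exception is in two places. Section 4.3 (Experimental group) foresees that "some journals will only provide the right to access and read manuscripts in the editorial management system, but not to send emails", and that in this case "the corresponding Editor (or designated person within the journal) will be informed to send the emails". Section 4.2 foresees limited access, under which "the emails from the intervention would be sent by a person from the editorial team".

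Section 4.7 (Randomisation and blinding) states "Editors will not be actively informed about the randomisation" and points in brackets to 4.3 as a possible exception. Section 4.1 carries no such qualification.

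On who is analysed, 4.8.1 says: "The main population for analysis will be all manuscripts randomised and accepted for publication in the participating journals". Section 4.4 lists first-round rejection, publication, and time from assignment of an academic editor to first decision as secondary outcomes.

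**The concern.** Under 4.3 the control arm gets no second email. A request to send one therefore tells the sender that the manuscript is in the C-short arm, and the email contains the ten items with their explanations (Appendix 1). The protocol does not require the sender to be someone other than the person deciding on that manuscript.

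If the two roles coincide, four things are at stake:

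- **What is tested.** The objective in 3.1 is the effect of asking peer reviewers. An editor with the checklist and knowledge of the arm could ask authors for the items directly.
- **Carry-over.** Randomisation is stratified by journal, so a fallback journal is expected to hold both arms. A sender who also handles control manuscripts could apply the items there.
- **Entry to the primary analysis.** Acceptance comes after randomisation and defines the analysis set. Someone who knows the arm could influence it.
- **Secondary outcomes.** Rejection, publication and time to first decision are themselves journal actions.

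**Working it through.** **1. The passages side by side**

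| Protocol section | Content | Consequence at a read-only journal |
|---|---|---|
| 4.1 | No journal-level contamination, because an outsider delivers the intervention | The premise fails: someone at the journal sends the email |
| 4.1 | Editors not actively told the allocation | Not met if the sender is an editor |
| 4.2, 4.3 | Sender is the corresponding Editor, a designated person, or a member of the editorial team | No condition on decision role |
| 4.3, control group | No second email | The request reveals the arm |
| 4.7 Randomisation and blinding | Exception acknowledged | No safeguard attached |
| 4.8.1 | Analysis set is accepted manuscripts | Depends on a journal decision made after randomisation |

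**2. The plan's own sample size (4.6)**

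Scenario 2 has 0.71 against 0.82, SD 0.25, two-sided alpha 0.05. Standardised difference = 0.11/0.25 = 0.44. The two-sample t-test needs 82.05 per arm for 80% power, so 83; power at 83 per arm is 0.805. Scenario 1 has 0.14/0.25 = 0.56, which needs 67.99 per arm, so 68, with power 0.900. Both stated sizes reproduce.

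**3. Carry-over to control manuscripts (illustration)**

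The protocol gives neither the share of manuscripts at fallback journals (f) nor the fraction of the contrast lost there (s). Both are assumptions. The diluted difference is 0.11 × (1 − f × s), and power is for 83 per arm with SD 0.25.

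| f | s | Difference | Power |
|---|---|---|---|
| 0 | 0 | 0.1100 | 0.805 |
| 0.10 | 0.25 | 0.1073 | 0.784 |
| 0.25 | 0.25 | 0.1031 | 0.752 |
| 0.25 | 0.50 | 0.0963 | 0.693 |
| 0.30 | 0.50 | 0.0935 | 0.668 |
| 0.50 | 0.50 | 0.0825 | 0.561 |

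**4. Arm-dependent selection (illustration)**

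Assume no true effect on any manuscript. Scores are drawn from a normal distribution with mean 0.71 and SD 0.25, with values outside 0 to 1 set to the nearer limit. A decision-maker who knows the arm rejects an extra share d of otherwise accepted C-short manuscripts, all from the poorer-reported half. With g the gap between the means of the upper and lower halves (0.367 by simulation), the mean among published C-short articles rises by d × g / (2 × (1 − d)):

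- d = 0.05: 0.05 × 0.367 / 1.90 = 0.0097, about 1.0 point
- d = 0.10: 0.10 × 0.367 / 1.80 = 0.0204, about 2.0 points
- d = 0.20: 0.20 × 0.367 / 1.60 = 0.0459, about 4.6 points

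The planned difference is 11 points. These figures suppose that every manuscript follows the fallback route; they shrink roughly in proportion to the share that does.

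The two mechanisms work in opposite directions, so the net bias has no known sign.

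**The case against.** The strongest reply is that this is a disclosed, contingent fallback. Section 4.7 points to it, 4.2 and 4.3 use it only where fuller access is refused, and it may seldom or never arise. The text already allows a designated person other than the Editor, and 4.2 plans detailed process discussions with each journal before it joins. The blinding was never firm either: editors are only not actively told, journals receive study information, and an editor may infer the arm from reviewers' requests. The email is worded as coming from the journal team, and section 1.3 hopes that journals will adopt the practice themselves, so a journal sender is close to intended use. All of this stands, and it limits the weight of the point.

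A reader might infer something stronger: that the handling editor will be unblinded, writes the decision letter, handles both arms, and so biases the primary result. The document does not support this. It does not define the corresponding Editor as the handling editor, Table 2 attributes the first decision to the journal, and stratification puts both arms in a journal, not under one editor. Nor is restriction to accepted manuscripts caused by the fallback. That selection exists under either sending route; the fallback only adds a way in which it could depend on knowledge of the arm.

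Disclosure does not answer two things: the unqualified statement in 4.1, and the absence of any rule keeping sender and decision-maker apart.

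**Conclusion.** The point holds as an unguarded exception and an over-broad statement. At read-only journals the protocol allows a member of the editorial team to learn the arm and hold the checklist, does not separate that person from decisions on the manuscript, and keeps in 4.1 a rationale that does not apply there.

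Harm follows only if the sender also takes part in decisions, which is neither stated nor excluded. Its size cannot be determined from the protocol. The illustrations run from a loss of about two points of power (0.805 to 0.784) to a substantial one (0.561), and selection could instead raise the difference by about 1 to 4.6 points if all manuscripts used this route. None of these is an estimate. A reader might take the 0.668 case as the expected power; it rests wholly on assuming 30% of manuscripts affected and half the contrast lost there.

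The stated sample size and power are correct for their inputs and need no change. This is a worthwhile, inexpensive improvement and not a defect that invalidates the design.

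**What to change.** 1. In 4.3 and 4.2, limit the fallback sender to a designated journal person who takes no part in decisions on that manuscript, and remove the corresponding Editor as a permitted sender. Settle this in the discussions with each journal already planned in 4.2.
2. Record the sending route for each journal.
3. In 4.1, confine the no-contamination statement to journals where the external researcher sends the email, and refer to the exception as 4.7 does.
4. Optionally, repeat the primary analysis without journals that could not comply. This may be left to the statistical analysis plan. It would have fewer than the planned number of articles if any journal were left out, so it serves as a check on the main result.

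The cost is a wording change using an option already in the text, plus one recorded field. The downside is that a journal without such a person must grant sending rights or be flagged as an exception.
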